## **6. Inclusion Criteria**

- 1) ultra-marathoners aged between 18 to 49 years
- 2) competing in the Sri-Chinmoy ultra-marathon race
- 3) no use of probiotics and antibiotics in the preceding 3 months
- 4) no history of acute or chronic illnesses.

## **7. Exclusion Criteria**

- 1) ultra-marathoners aged < 18 or > 49 years
- 2) not competing in the Sri-Chinmoy ultra-marathon race
- 3) use of probiotics and antibiotics in the preceding 3 months
- 4) history of acute or chronic illnesses.

## **8. Primary Outcomes**

1. Intestinal microbial adaptation according to applied diet evaluated by analysing faecal samples taken seven days before and seven days after the race using shotgun metagenomic analysis.

## **9. Secondary Outcomes**

1. Oxidative stress and muscle fatigue-related biomarkers measured using blood samples immediately before, at the end of 0 h, 2 h and 24 h of the race.

## **10. Material and Methods**

### **Preliminary Tests**

Following full verbal and written explanation of the study procedures, participants will be asked to sign an informed consent form. After the enrollment of the study, research data will be collected from the participants at four steps (three visits to the laboratory and the race day) throughout the study. At the first visit (seven days before the race), participants will be invited to the exercise metabolism laboratory. Participants will be informed to come to the laboratory in a fasted state. Fecal samples will be collected using fecal sample collection and preservative kit. Anthropometric measurements (body weight, height and fat-free mass) will be collected. An extended research questionnaire will be administered by research staff. Triaxial accelerometry will be attached to the participants' waist, and will be secured with an elastic belt. The device will be worn continuously throughout the entire study period (seven days before and seven days after the race), except during activities that would submerge the accelerometer in water or if removed for legitimate reasons (e.g., discomfort during sleep). Participants will be informed about how to keep detailed food and liquid diary and will be asked to keep dietary data throughout the study period (14 days). At the same time, a detailed activity log (activity, time and duration) will be kept for the participants.

The second visit will be performed within three to seven days before the race to measure maximum oxygen consumption using indirect calorimetry (Viasys Jager Master Screen CPX, PanGas AG, Dagmarsellen, Switzerland). Participants will be advised to follow their normal diet and to avoid strenuous exercise/ sports 24 hours before the VO2max test. Heart rate will be measured continuously by a heart rate monitor (Polar-S-810 heart rate monitor), and respiratory variables will be recorded every 30 s.

### **Pre-Race**

Before starting the ultra-marathon race, body weight will be measured using a commercial scale. Blood samples will be drawn from an antecubital vein (two tubes/20 ml). The blood samples will be kept on ice until it can be analyzed.

### **Post-Race**

Body weight will be measured and all food and liquid consumption during the race will be recorded by the dietician immediately after the race. Blood samples (two tubes / 20 ml) will be drawn at three points Post-Race: i) immediately after the race, ii) at 2 and iii) 24 hours after the end of the race. Participants will visit the laboratory to give blood samples 24 hours after the race (third visit).

Fecal samples will be collected from the participants' at the fourth visit. During this visit, all dietary data will be verified by the dietician.

## **10. 1. Data Collection Tools**

### **Research Questionnaire**

Participants will complete the extended research questionnaire which was applied in the NURMI study by Wirnitzer et al [32]. An extended research questionnaire form mainly includes questions related to health status, exercise/sports history (number of completed ultra-marathon competitions, year of first race, and number of training hours per week, etc.), diet patterns before, during and after race. Additionally, the Physical Activity Readiness Questionnaire (PAR-Q) will be applied to determine current cardiovascular health [33]. Results of the questionnaires will be analyzed using SPSS statistic program version 23.0 (IBM, Armonk, NY).

### **Body Composition Assessment**

To assess body composition of participants, they will be asked to visit the research laboratory in a fasted state (after an overnightfast) and refrain from caffeine (at least four hours), alcohol (at least two hours), cigarette (at least two hours), and not to exercise at high intensity for 24 hours before the visit.

Body weight and fat-free mass will be measured using a commercial scale Beurer BF 15 (Beurer GmbH, Ulm, Germany) with 0.1 kg accuracy. Height will be measured while participants are standing, head positioned in Frankfurt horizontal plane, using a portable stadiometer (Seca 213, Hamburg, Germany). Bone mineral density and body fat percentage will be measured using dual-energy X-ray absorptiometry (DXA).

### **Energy Availability**

Individual RMR was estimated using the Mifflin-St. Jeor equation [34], as validated in ultra-endurance athletes previously [35].

All participants will be asked to keep a detailed activity logs (time, intensity, and duration) seven days before- and seven days after the race. Activity logs will provide the information on the intensity and duration of physical activity and training to calculate exercise energy expenditure (EEE) [36]. Corrected Metabolic Equivalent (MET) values from the Compendium of Physical Activities will be used to estimate the EEE recorded in the activity logs [37]. As previously stated by Guebels et al [38], only activities with an intensity greater

than 4.0 METs will be included in the calculation. EEE is the sum of all exercises multiplied by the activity hours and FFM. EEE will be adjusted to remove the calories contributed by RMR for the duration of exercise [39] by subtracting RMR energy expenditure per hour of all activities reported at 4.0 METs or higher from the total EEE.

Participants will be informed about how to keep detailed food and liquid diary and will be asked to keep dietary data throughout the study period. Energy intake will be determined by the dietician using food and fluid records and analyzed with the Swiss Food Composition Database [40].

Energy availability will be calculated according to the formula below;

Energy intake - adjusted energy expenditure/ fat-free mass (kg)

Recommended energy availability for athletes is defined as approximately 45 kcal.kg and <30 kcal.kg is defined as low energy availability [41].

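### The exercise-energy rule uses two different MET thresholds and nets a whole-body RMR off an FFM-scaled cost; under the usual MET definition this overstates energy availability

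*Protocol*

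**What the plan says.** All the rules stand under Energy Availability in Protocol section 10.1.

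- **RMR:** "Individual RMR was estimated using the Mifflin-St. Jeor equation". This gives a whole-body figure in kcal per day.
- **MET values:** "Corrected Metabolic Equivalent (MET) values from the Compendium of Physical Activities will be used to estimate the EEE recorded in the activity logs". The correction is not defined, and no energy value per kg is given for one MET.
- **Gross exercise energy expenditure (EEE):** "EEE is the sum of all exercises multiplied by the activity hours and FFM".
- **Which activities count:** only those with an intensity greater "than 4.0 METs will be included in the calculation".
- **Netting:** the adjustment is made by "subtracting RMR energy expenditure per hour of all activities reported at 4.0 METs or higher from the total EEE".
- **Energy availability (EA):** printed as "Energy intake - adjusted energy expenditure/ fat-free mass (kg", with nothing bracketing the difference.
- **Reference values:** "Recommended energy availability for athletes is defined as approximately 45 kcal.kg", with values below 30 classed as low.

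Fat-free mass (FFM) comes from the Body Composition Assessment: "Body weight and fat-free mass will be measured using a commercial scale Beurer BF 15". Energy availability is part of aim 3 in section 2. It is not named among the primary or secondary outcomes in sections 8 and 9.

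**The concern.** Two features of the rule change the result.

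First, the inclusion sentence and the netting sentence draw the line at 4.0 METs differently. An activity logged at exactly that value falls outside the gross sum but inside the RMR subtraction, so it contributes negative expenditure.

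Second, gross cost is scaled to fat-free mass while the resting cost removed from it belongs to the whole body. If a MET is a multiple of whole-body resting cost, the gross term is too small, net expenditure is too small, and energy availability is too high.

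What is at stake is the description of participants against 45 and 30 kcal/kg. With ten participants per group (section 5), one person moved across 30 changes that group's proportion with low availability by 10 percentage points.

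**Working it through.** The protocol gives no worked energy-availability value, so there is no figure to reproduce. The check applies the written rule to assumed participants.

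**Assumptions not in the protocol.** Man: 70 kg, 175 cm, 35 y, 10–20% body fat. Woman: 57 kg, 165 cm, 35 y, 18–25% body fat. Exercise: 8–12 METs for 1–2 h/day. Base case: 1 MET = 1 kcal per kg body mass per hour.

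**RMR from the named equation.**
- Man: 10×70 + 6.25×175 − 5×35 + 5 = 1623.75 kcal/day, or 67.7 kcal/h.
- Woman: 10×57 + 6.25×165 − 5×35 − 161 = 1265.25 kcal/day, or 52.7 kcal/h.

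**Threshold.** Take one hour at exactly 4.0 METs for the man with 15% fat (FFM 59.5 kg).
- As written: gross 0, RMR removed 67.7 kcal, so EA rises by 67.7/59.5 = 1.14.
- Left out of both terms: no change.
- Counted in both, still on FFM: (4×59.5 − 67.7)/59.5 = 2.86, so EA falls by 2.86.

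Over all five cases below, the rise is 1.07 to 1.23 and the fall 2.77 to 2.93.

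**Mass basis.** As written, net EEE = MET × h × FFM − (RMR/24) × h. On body mass, it is MET × h × body mass − (RMR/24) × h. The RMR terms cancel in the difference. With *f* the body-fat fraction:

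shift in EA = MET × h × (body mass − FFM)/FFM = MET × h × f/(1 − f)

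Example (man, 15% fat, 10 METs, 2 h): 1190 − 135 = 1055 kcal as written, against 1400 − 135 = 1265 kcal. The shift is 210/59.5 = 3.5, so a participant at 28 on the body-mass basis would be reported at 31.5.

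**Sensitivity to *Corrected*.** Suppose it means MET × 3.5 / (the person's RMR in ml/kg/min), at 5 kcal per litre of oxygen. The factor *c* is 1.086 for the man and 1.135 for the woman. Compared with an uncorrected MET times body mass, the shift becomes MET × h × [1/(1 − f) − c].

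| Case | FFM (kg) | Shift, standard MET | Shift, RMR-corrected MET |
|---|---|---|---|
| Man, 10% fat | 63.0 | 0.9 to 2.7 | 0.2 to 0.6 |
| Man, 15% fat | 59.5 | 1.4 to 4.2 | 0.7 to 2.2 |
| Man, 20% fat | 56.0 | 2.0 to 6.0 | 1.3 to 3.9 |
| Woman, 18% fat | 46.74 | 1.8 to 5.3 | 0.7 to 2.0 |
| Woman, 25% fat | 42.75 | 2.7 to 8.0 | 1.6 to 4.8 |

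Units are kcal/kg FFM/day. The lower value is 8 METs for 1 h, the upper 12 METs for 2 h.

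**A comparator without the body-mass assumption.** If gross cost is MET × RMR/24 × h, using the protocol's own RMR, the shift is MET × h × [(RMR/24)/FFM − 1]. The bracket runs from 67.7/63.0 − 1 = 0.07 to 52.7/42.75 − 1 = 0.23. The shift is then 0.6 (8 METs, 1 h) to 5.6 (12 METs, 2 h).

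**Brackets.** For the man with 15% fat at 10 METs for 1 h, net EEE is 527 kcal. With an intake of 2,500 kcal, (2500 − 527)/59.5 = 33.2, while the formula read literally gives 2500 − 527/59.5 = 2491.

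**The case against.** The strongest reply is that FFM scaling is one stated rule, not a contradiction. The protocol nowhere says that a MET is per kg of body mass, and it calls its MET values corrected without saying how. That stands: the size of the overstatement is conditional, and part of it could already be absorbed by the correction. The mismatch in the resting term alone is small, 0.07 to 0.23 kcal/kg FFM per hour. The larger figures come from the gross term.

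Several stronger readings are tempting, and the protocol does not support them.

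- **That all three features bias energy availability upward.** The missing brackets do not. The kcal/kg reference values make the intended quotient plain, and nobody would report a value near 2,500. This is notation.
- **That the threshold clash matters widely.** It touches only activities logged at exactly 4.0 METs, and nothing in the protocol suggests that these are a large share of an ultra-marathoner's exercise.
- **That the rule yields negative costs at rest.** One MET times FFM is indeed below hourly RMR (59.5 against 67.7 kcal/h for the man with 15% fat), but activities at that intensity are never entered.
- **That the vegan–omnivore comparison is biased.** Both groups are scored by the same rule. The contrast is distorted only if body fat or exercise load differs between them, and the protocol gives no figures on either.

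**Conclusion.** The point holds in limited form. The two thresholds conflict outright, and an hour at exactly 4.0 METs raises energy availability by about 1.1 kcal/kg FFM compared with leaving it out of both terms. The gross and resting terms are on different bases. Under the usual body-mass definition of a MET, the written rule overstates energy availability by about 0.9 to 8.0 kcal/kg FFM/day in the cases tried, or about 0.2 to 4.8 if the METs are RMR-corrected. The direction was upward in every case. The size depends on body fat, training load and the meaning of *Corrected*, so an unconditional claim of material bias would go too far.

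The practical consequence is that a participant somewhat below 30 may be reported above it. Severity is moderate. Energy availability is a stated aim but not a listed outcome, and the protocol ties no test or eligibility rule to the cut-offs.

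**What to change.** 1. Use one MET inclusion threshold for both the gross sum and the RMR subtraction. The sponsor should reconcile which of the two stated thresholds applies.
2. Define the MET correction and put gross cost on the same whole-body basis as the RMR removed: MET × hours × body mass, or MET × RMR/24 × hours. The choice should follow the definition. Under the correction assumed above, multiplying a corrected MET by body mass would raise gross cost by about 9 to 14% (factors 1.086 and 1.135) over an uncorrected MET times body mass.
3. As a notation correction, write EA = (energy intake − adjusted EEE)/FFM, in kcal per kg FFM per day.

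The cost is wording and a spreadsheet formula; no new data are needed. Reported energy availability will be somewhat lower than under the present rule.

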### **Maximum Oxygen Consumption measurement**

The maximum oxygen consumption (VO2max) will be measured using indirect calorimetry (Viasys Jager Master Screen CPX, PanGas AG, Dagmarsellen, Switzerland) by the method used in a previous study on male runners by Shing et. al [42]. The method includes an incremental running test performed on treadmill. The test protocol will start at 10 km h, 0% gradient with the speed increasing by 1 km h each minute until a speed of 18 km h. After 1 min at 18 km h, the treadmill gradient will be increased by 1% each minute until volitional fatigue. Heart rate will be continuously measured Polar-S-810 heart rate monitor respiratory variables will be recorded every 30 s. Perceived exertion will be evaluated using Borg Scale 6 to 20 [43]. Higher score indicates higher exhaustion.

### **Fecal sample collection**

Fecal samples will be collected at two time points (seven days before and seven days after the race). The feces sample collection kit (Fe-Col® Faecal Sample Collection Kits, UK) will be provided to the participants. They will be told about the feces collection protocol, described in detail by Wu et al. [44]. They will be required to bring the stool samples to the laboratory within the 45 minutes after collection. After stool samples will be delivered to the researchers, they will be first stored at -20 oC for 24 hours, then will be delivered -80 oC before the whole metagenomics analysis.

### **Blood parameters**

Blood samples will be collected at four time points (immediately before- and immediately after the race, two and 24 hours after the end of the race). Plasma MDA, TAC (measured by FRAP assay), d-ROMs and HSP-70 will be analyzed to determine oxidant / antioxidant capacity. Serum ORM-1 will be analyzed to assess exercise-induced fatigue.

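### No plasma-volume marker is listed and the on-ice rule has no time limit, so the blood-marker time course cannot be separated from fluid shifts and may not be separable from storage time

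*Protocol*

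**What the plan says.** Section 9 of the protocol lists one secondary outcome, timed relative to the race: "Oxidative stress and muscle fatigue-related biomarkers measured using blood samples immediately before, at the end of 0 h, 2 h and 24 h of the" […]. The Blood parameters part of section 10.1 repeats the four draws and fixes the panel. Four markers are measured in plasma: "Plasma MDA, TAC (measured by FRAP assay), d-ROMs and HSP-70 will be analyzed to determine oxidant / antioxidant capacity". One is measured in serum: "Serum ORM-1 will be analyzed to assess exercise-induced fatigue". No haematocrit, haemoglobin, total protein or other indicator of plasma volume appears there or elsewhere in the protocol.

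The only rule on handling blood stands under Pre-Race in section 10: "The blood samples will be kept on ice until it can be analyzed". The Post-Race text gives no handling rule for the other three draws. It does place the last draw elsewhere: "Participants will visit the laboratory to give blood samples 24 hours after the race (third visit"). Each draw is two tubes, 20 ml.

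The fluid-related data that are collected are a weight before the start ("Before starting the ultra-marathon race, body weight will be measured using a commercial scale"), a weight and an intake record at the finish ("Body weight will be measured and all food and liquid consumption during the race will be recorded by the dietician immediately after the race"), and a food and fluid diary over the 14 study days.

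**The concern.** A marker measured per volume of plasma or serum moves when plasma volume moves, even if the circulating amount stays the same. Here the samples span an ultra-marathon and the first day of recovery, a period in which fluid balance can be expected to change. Without a plasma-volume marker at each draw, a rise at the finish or a fall at 24 h can be read as oxidative stress, antioxidant response or fatigue when part or all of it is concentration or dilution.

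The ice rule adds a second possible source of change. It has no end point, so it allows the time between draw and assay to differ systematically from one time point to the next. Stability on ice would then be mixed into the same time course.

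At stake is the interpretation behind aim 4 in section 2 and the second paragraph of section 13, where these markers stand for oxidant/antioxidant balance and fatigue. The plasma-volume gap lies in data collection. Once the race has been run, no later analysis document can close it.

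**Working it through.** The protocol states no plasma-volume figure, storage time or SD for the blood markers, so there is no figure of its own to reproduce. What follows is an illustration. The sampling scheme and group sizes are the protocol's. The plasma-volume changes and race durations are assumptions.

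**1. Fluid shift within a group.** Let dPV be the fractional change in plasma volume since the pre-race draw. With a constant circulating amount, concentration is amount divided by volume, so

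apparent change = 1/(1 + dPV) − 1.

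| Assumed dPV | Calculation | Apparent change, no true change |
|---|---|---|
| −5% | 1/0.95 − 1 | +5.3% |
| −10% | 1/0.90 − 1 | +11.1% |
| +10% | 1/1.10 − 1 | −9.1% |
| +20% | 1/1.20 − 1 | −16.7% |

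If plasma volume fell by the finish and rose above its starting value by 24 h, every marker would appear to go up and then down together.

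**2. Fluid shift and the diet contrast.** On a ratio (log) scale, the artefact in the vegan-to-omnivore comparison of changes is

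ratio of ratios = (1 + dPV in group B)/(1 + dPV in group A).

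| Group A | Group B | Ratio of ratios |
|---|---|---|
| −10% | −10% | 0.90/0.90 = 1.000 |
| −10% | −5% | 0.95/0.90 = 1.056 |
| −10% | 0% | 1.00/0.90 = 1.111 |
| −10% | +10% | 1.10/0.90 = 1.222 |

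A shift common to both groups cancels. Only a difference between groups leaves a bias.

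**3. Storage time.** The protocol does not say when the assays are run. Two readings fit its text:

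- *Each draw is processed promptly.* Time on ice then differs by about 0 h between time points.
- *All samples are assayed together at the 24 h draw.* With race duration D, the tubes wait D + 24 h (pre-race), 24 h (finish), 22 h (2 h) and 0 h (24 h). For assumed D of 6, 12 or 24 h, the pre-race tube waits 30, 36 or 48 h.

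Under the second reading, waiting time follows sampling time exactly. How much each marker drifts on ice is not in the document, so no percentage can be attached.

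**4. Can the collected data stand in for a plasma-volume marker?** Weight is recorded just before and just after the race; none is stated at 2 h or 24 h. The before-to-after weight change also includes food eaten during the race. The diary covers intake, not fluid loss. These data can help show whether the groups differ in fluid balance up to the finish. They do not give dPV at any draw.

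**5. Handling of the other specimen.** Under Fecal sample collection, stool must reach the laboratory within 45 minutes and is stored at −20 °C for 24 hours and then at −80 °C. Blood has no corresponding limits.

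**6. Materiality.** With ten runners per group (section 5), and assuming two-sided 5% significance, 80% power and a normal approximation, the detectable difference between groups is √(2/10) × (1.960 + 0.842) = 1.25 SD. The detectable change within a group is (1.960 + 0.842)/√10 = 0.89 SD of the paired difference. Since no SD is given, the percentages above cannot be put on this scale.

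**The case against.** The strongest reply is that the protocol does not say the things most easily read into it.

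- **Uncorrected comparison.** A reader might infer that the markers will be compared as raw concentrations. The Blood parameters text is a list of analytes, and section 11 describes no analysis of them. How they are compared may properly be left to a statistical analysis plan. This stands: no analysis choice can be faulted. It does not reach the missing measurement, because a plan cannot correct for a volume change nobody measured.
- **Unequal storage.** A reader might infer that pre-race tubes sit on ice through the whole race. The text permits this but does not prescribe it, and naming plasma and serum implies a separation step. This also stands. What remains is that the step has no time, no freezing and no batch rule, and that the ice sentence appears only under Pre-Race.
- **The diet comparison.** A shift common to both groups cancels on the ratio scale, and the documents do not show that fluid shift or handling differs by diet. This stands, and it confines the certain harm to the within-group time course. Aim 3 does set out to compare intake before, during and after the race, so a difference between groups is possible, but it is not established.
- **Existing fluid data.** Weights, race intake and diaries allow a partial check up to the finish. They do not replace a plasma-volume marker at 0, 2 and 24 h.
- **Assumed magnitudes.** The plasma-volume changes, race duration and stability on ice are not in the protocol. The arithmetic is sound, but its inputs are illustrative.

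**Conclusion.** The point holds in a limited form. The secondary outcome is a time course of plasma and serum measurements across an ultra-marathon. As listed, the measurements do not allow change within a diet group to be separated from fluid shifts. Because the ice rule is open-ended, that change may also not be separable from storage time.

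The size is conditional. If plasma volume fell by 5% to 10%, every marker would appear to rise by 5.3% to 11.1%. If it rose by 10% to 20%, every marker would appear to fall by 9.1% to 16.7%. The vegan-omnivore contrast is unaffected by an equal shift. A 10% fall in one group against a 5% fall in the other would give a ratio of 1.056.

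The documents do not support the stronger conclusions that the plan prescribes uncorrected comparisons or unequal holding times, or that the diet contrast is biased as it stands. Nor do they require that corrected values be the main analysis; that is a matter of preference. I would label this a cheap improvement. The plasma-volume part has to be settled before the race, because it cannot be recovered afterwards.

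**What to change.** **Blood parameters (section 10.1).** Add haematocrit and haemoglobin, measured on whole blood at each of the four draws already planned. If circulating haemoglobin is taken as constant, blood volume is inversely proportional to haemoglobin concentration, so

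1 + dPV = (Hb before/Hb after) × (1 − Hct after)/(1 − Hct before).

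Multiplying a post-race concentration by this factor refers it to the pre-race plasma volume. Report corrected and uncorrected values side by side.

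**Pre-Race and Post-Race (section 10).** Replace the open-ended ice rule with one that covers all four draws: one fixed maximum time from draw to plasma or serum separation, then freezing, with each runner's four samples assayed in the same batch. Record the actual times.

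**Cost.** One routine blood-count result per draw, and a centrifuge and cold storage at the race. No extra venepuncture is needed. Tube types are not given in the protocol, so the laboratory should confirm that one of the two tubes is suitable for a blood count. The downside is modest field logistics.
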